## Abstract

**Background:**

Age-related macular degeneration (AMD), a leading cause of irreversible vision impairment in the United States and globally, is a disease of the photoreceptor support system involving the retinal pigment epithelium (RPE), Bruch’s membrane, and the choriocapillaris in the setting of characteristic extracellular deposits between outer retinal cells and their blood supply. Research has clearly documented the selective vulnerability of rod photoreceptors and rod-mediated (scotopic) vision in early AMD, including delayed rod-mediated dark adaptation (RMDA) and impaired rod-mediated light and pattern sensitivity. The unifying hypothesis of the Alabama Study on Early Macular Degeneration (ALSTAR2) is that early AMD is a disease of micronutrient deficiency and vascular insufficiency, due to detectable structural changes in the retinoid re-supply route from the choriocapillaris to the photoreceptors. Functionally this is manifest as delayed rod-mediated dark adaptation and eventually as rod-mediated visual dysfunction in general.

**Methods:**

A cohort of 480 older adults either in normal macular health or with early AMD will be enrolled and followed for 3 years to examine cross-sectional and longitudinal associations between structural and functional characteristics of AMD. Using spectral domain optical coherence tomography, the association between (1) subretinal drusenoid deposits and drusen, (2) RPE cell bodies, and (3) the choriocapillaris’ vascular density and rod- and cone-mediated vision will be examined. An accurate map and timeline of structure-function relationships in aging and early AMD gained from ALSTAR2, especially the critical transition from aging to disease, will identify major characteristics relevant to future treatments and preventative measures.

**Discussion:**

A major barrier to developing treatments and prevention strategies for early AMD is a limited understanding of the temporal interrelationships among structural and functional characteristics while transitioning from aging to early AMD. ALSTAR2 will enable the development of functionally valid, structural biomarkers for early AMD, suitable for use in forthcoming clinical trials as endpoint/outcome measures. The comprehensive dataset will also allow hypothesis-testing for mechanisms that underlie the transition from aging to AMD, one of which is a newly developed Center-Surround model of cone resilience and rod vulnerability.

**Trial registration:**

ClinicalTrials.gov Identifier NCT04112667, October 7, 2019.

## Background

Age-related macular degeneration (AMD) is a leading cause of irreversible central vision impairment in the world [1]. It is a disease of the photoreceptor support system involving the retinal pigment epithelium (RPE), Bruch’s membrane (BrM), and choriocapillaris (ChC), in the setting of characteristic extracellular deposits between outer retinal cells and their blood supply. This pathology impacts retinoid re-supply, leading to photoreceptor demise and vision loss [2]. During the last several decades research has clearly documented the selective vulnerability of rod photoreceptors in the macula and rod-mediated (scotopic) vision during aging and early AMD as compared to cone photoreceptors and cone-mediated vision [3–11]. Several important findings lay down an innovative platform for our proposed research program. Rod-mediated dark adaptation (RMDA) is delayed in early AMD in that there is slowing in the recovery rate of light sensitivity after exposure to a bright light [6, 12]. Steady state rod-mediated light sensitivity, i.e., sensitivity to light after the retina adapts to a very low light level, is also impaired [5, 13–15]. We identified in a prospective study that delayed RMDA is the first-ever functional biomarker (risk factor) for incident early AMD [16]. Furthermore, we showed that those with high-risk ARMS2 and CFH sequence variants are more likely to have delayed RMDA [17]. RMDA also tracks progression through intermediate AMD in longitudinal studies, and it has been incorporated into large observational studies [18–20].

This report describes the recently-initiated Alabama Age-related Maculopathy Study 2 (ALSTAR2), a multi-disciplinary prospective study to establish a structural basis of RMDA delay and scotopic impairment in older adults at-risk for AMD and those who have already converted to early AMD. We will elucidate coincident structural and functional mechanisms underlying the transition from normal aging to AMD, and thus, mechanisms of disease initiation that will inform theories and models of early AMD pathogenesis. Results will also inform new endpoints for clinical trials evaluating early AMD treatments. In a large cohort of older adults who at baseline have either normal macular health or early AMD, we will assess structure using optical coherence tomography (OCT; spectral domain and OCT angiography), quantitative fundus autofluorescence (qAF), and scotopic function using RMDA and steady-state scotopic light sensitivity after adaptation to a dark background. Structure-function relationships will be examined cross-sectionally, topographically, and longitudinally, over 3 years. Our unifying hypothesis across all aims is that to the photoreceptors, early AMD is a disease of the retinoid re-supply route from plasma, due to detectable structural changes in the choriocapillaris-Bruch’s membrane-RPE complex (independent variables) which manifest functionally as delayed RMDA (dependent variable). In this model RMDA is also a measurable indicator for many molecular transfers occurring across this interface that if impaired may lead to additional metabolic and/or micronutrient insufficiencies.

The specific aims of ALSTAR2 are:
In AMD, the presence of extracellular deposits in the macula – soft drusen and subretinal drusen deposits (SDD, a.k.a reticular pseudodrusen) – increase AMD progression risk and compromise metabolic exchange between the ChC and outer retinal cells. Our hypothesis is that scotopic dysfunction will be accentuated where drusen and/or SDD are present, with SDD having a greater negative impact than drusen on scotopic function both cross-sectionally and prospectively.RPE cell bodies lose epithelioid morphology before anterior migration or apoptosis, as evidenced by variability and thickening of the RPE band in OCT and dimming of fundus autofluorescence signal from organelles believed to contain bis-retinoids. The thickness of photoreceptor- and RPE-attributable reflective bands will be assessed for context. Our hypothesis is that variability in RPE cell bodies is associated more strongly with scotopic dysfunction than photopic function both cross-sectionally and prospectively.The vascular density of the ChC (proportion of BrM covered) is a measure of direct metabolic exchange capacity between plasma and outer retinal cells in aging and early AMD. ChC vascular density declines in aging, under individual drusen, and in complete RPE and outer retinal atrophy (cRORA; geographic atrophy) [21]. Our hypothesis is that decreased ChC vascular density is more strongly associated with scotopic dysfunction than photopic function both cross-sectionally and prospectively.

### Public health significance

AMD is a complex, multi-factorial disease of aging in which central retinal photoreceptors are ultimately lost by a neovascular event or an atrophic process or both. About 14 million Americans have AMD, and this number is increasing. AMD generates significant personal burden due to reading and driving difficulties, depression, and anxiety [22–24]. Proven strategies for reducing AMD burden focus on preventing or stabilizing end-stage neovascularization with anti-vascular endothelial growth factor therapy, rightfully hailed as major scientific and medical breakthroughs [25–27]. Yet the vast majority of Americans with AMD have early disease. Currently there are neither proven means to arrest the progression of early AMD, nor prevention strategies for those at high risk.

A barrier to developing preventative and therapeutic strategies is a limited understanding of how aging, AMD’s largest risk factor, transitions to early AMD. Equally important is lack of valid and responsive endpoints acceptable to both the US Food and Drug Administration (FDA) and the scientific community [28, 29]. Anatomical (structural) endpoints are favored in clinical trials due to the speed, objectivity, and comprehensiveness of modern retinal imaging. Of these, the most promising will be those that correlate with visual function, facilitating use as primary outcome or surrogate measures. Thus, there is an urgent need to focus on precursors of early disease in order to understand the mechanisms underlying the earliest emergence of AMD and also to identify structural endpoints that can be functionally validated, i.e. structural and functional endpoints that are associated with each other.

### Background in physiology and aging

The human retina is overall dominated by rod photoreceptors over cones (rod:cone ratio, 21:1). Because AMD’s debilitating vision loss affects central vision, we emphasize that the macula is also rod-dominated, despite the presence of the fovea, according to histologic studies using computer-assisted flat mounts to ensure accurate and unbiased counts [3, 30] and then validated in vivo with single-cell imaging [31]. “Macula” is variably defined, and Table 1 shows photoreceptor content in subfields of the Early Treatment of Diabetic Retinopathy Study (ETDRS) grading grid, widely used to assess AMD prevalence, incidence, and severity by color fundus photography. In this grid, rods outnumber cones 8.7:1 in younger adults and 6.8:1 in younger adults. The central 1 mm diameter subfield contains the cone-only foveola (0.375 mm in diameter) and a few rods around its rim, accounting for the non-zero rod: cone ratio in Table 1. In younger and older adults, respectively, mean rod density is 4.2-fold and 3.2-fold higher than cones in the inner ring (para- and perifovea), and 12.9-fold and 10.1-fold higher in the outer ring (perifovea) [32, 33]. These studies showed that in aging macula, rods die before cones, in a parafoveal ring directly surrounding the fovea, where loss is 30% up to age 92 (Fig. 1a-c). Further, histology also revealed that the last photoreceptors surviving in late AMD are cones [3, 4]. A monotonic trajectory of greater loss of rods than cones, beginning in aging, is a parsimonious explanation for these data. It is important to note that the highest densities of rods are outside the ETDRS grid in an elliptical ring at 2–5 mm eccentricity and extending into the nasal retina. The principal signal source for FAF imaging (Aim 2) is RPE lipofuscin, long-lasting inclusion bodies within these cells, and this tracks photoreceptor topography precisely, with highest intensities overlying the rod ring [36]. Thus, parafoveal rod loss in aging is spatially uncorrelated with highest levels of lipofuscin-attributable autofluorescence, as noted [3].

**Table 1 Tab1:** Photoreceptor density (cells/ mm^2^) in human macula [3, 30]

ETDRS subfields (inner to outer radius in mm and degrees of visual angle)	Mean cells/ mm^2^ in subfield		Ratio of Rods to Cones
	Cones/ mm^2^	Rods/ mm^2^	Rods : Cones
	Ages 27-37 years		
Center (0 - 0.5 mm; 0 - 1.7°)	57,001	20,013	0.35
Inner (0.5 - 1.5 mm; 1.7 - 5.2°)	18,774	78,252	4.17
Outer (1.5 - 3.0 mm; 5.2 - 10.4°)	10,138	130,750	12.90
Mean photoreceptor density in ETDRS grid	13,354	116,037	8.69
	Age 61-90 years		
Center (0 - 0.5 mm; 0 - 1.7°)	54,897	15,016	0.27
Inner (0.5 - 1.5 mm; 1.7 - 5.2°)	17,673	56,105	3.17
Outer (1.5 - 3.0 mm; 5.2 - 10.4°)	9,512	96,265	10.12
Mean photoreceptor density in ETDRS grid	12,582	85,106	6.76
**RMDA test spot locations**	Ages 27-37 years		
5° superior	15,530	82,357	5.30
12° superior	9,406	145,683	15.49
	Ages 61-82 years		
5° superior	15,376	62,043	4.04
12° superior	8,835	116,683	13.21

1 mm = 3.5° visual angle

The ETDRS grid is 28.27 mm^2^ in area and contains 377,530 cones and 3,280,371 rods in retinas of donors aged 27-37 and 355,678 cones and 2,405,952 rods in retinas from donors aged 61-90. Densities at specific locations were determined by finely space resample of the original data

*ETDRS* Early Treatment of Diabetic Retinopathy Study, *RMDA* Rod-mediated dark adaptation

**Fig. 1 Fig1:**
[figure not shown]
Aging of the human photoreceptor mosaic and the outer retinal neurovascular unit. A-C Rod vulnerability and cone resilience in healthy aging [34, 35]. Topography of rods and cones determined from computer-assisted cell counts in flat-mounts of human retina [3]. Maps are shown as a fundus of a left eye. Black oval, optic nerve; black ring, outer limit of Early Treatment of Diabetic Retinopathy Study grading grid. A1, A2. Rods and cones in 27–37-year-old donors. B1, B2. Rods and cones in 82–90-year-old donors. C1, C2. Log mean difference in cell density between younger and older adults. C1. Difference in rod density between younger and older adults is greatest at 0.5 mm to 3 mm from fovea (parafovea and perifovea). Purple signifies that aged eyes had 31% fewer cells than young eyes. C2. Log mean difference in cone density between younger and older adults is small and inconsistent, indicated by the yellow-green map. D Outer retinal neurovascular unit and retinoid re-supply to cone and rod photoreceptors. Shown are rods (R), cones (C), Müller glia (M), RPE, and vascular endothelium of the choriocapillaris (ChC) and capillary plexuses of the retinal circulation. We hypothesize that to the photoreceptors, AMD is a disease of the retinoid re-supply route. Vitamin A delivered from plasma is rate-limiting for recovery of sensitivity by rods. Rods need choriocapillaris, Bruch’s membrane, and RPE, whereas the cones have these, plus an additional second delivery route, via Müller glia and the retinal circulation. RMDA assesses how pathology in the choriocapillaris, Bruch’s membrane, and RPE complex impacts rods. It is expected that cone-mediated vision will be resilient. Retinal layers: ILM, inner limiting membrane; NFL, nerve fiber layer; GCL, ganglion cell layer; IPL, inner plexiform layer; INL, inner nuclear layer; OPL, outer plexiform layer; ONL, outer nuclear layer; ELM, external limiting membrane; RPE, retinal pigment epithelium; BrM, Bruch’s membrane; ChC, choriocapillaris

RMDA assesses the efficiency of replenishing retinoids and loading of 11-*cis*-retinal to the opsin molecule in rod outer segments, as established by a landmark quantitative analysis [37–39] incorporating fundus reflectometry, visual cycle biochemistry, and clinical observations of sensitivity recovery in outer retinal disease. The visual cycle is the process of eliminating products of light absorption from outer segments, recycling of released retinoid to its original form (11-*cis*-retinal), and regenerating the visual photopigment opsin [37, 38]. The RPE serves photoreceptors in many ways, including the delivery of fresh 11-*cis*-retinal, uptake and translocation of nutrients and hormones, phagocytosis of spent OS tips, and elimination of unneeded metabolites. Cones are also served by the RPE and choriocapillaris, but due to a second visual cycle (in Müller glia), which depend on retinal circulation [40, 41], they are less vulnerable to ChC-BrM-RPE pathology than are rods, at least in early AMD stages. On the basis of our prior prospective study (ALSTAR 1), we hypothesize that to the photoreceptors, AMD is a disease of the retinoid re-supply route to rods, directly implicating changes in essential structures external to the outer segments (ChC endothelium, BrM, RPE; Fig. 1d).

A strong point of the ALSTAR2 design is the incorporation of new concepts in outer retinal physiology and importantly, the biology of soft drusen, the earliest discovered and largest risk factor for progression to AMD end stages (odds ratio for progression risk at 10 years = 26) [42–45]. The vertically organized and tightly integrated physiologic unit of photoreceptors, Müller glia, RPE, ChC, and deep capillary plexus can be considered the outer retinal neurovascular unit (Fig. 1d) [46]. This construct, developed originally for brain and then inner retina [47, 48] comprises micro-vessels, neurons, glia, pericytes, and extracellular matrix that couple blood flow to the metabolic demands of neurons. AMD can be conceived as either a neurodegeneration or a disease of vascular/metabolic insufficiency, depending on the initial site of damage. Marked histologic aging alterations in human retina are the buildup of a lipid-rich barrier in macular BrM and a decline in ChC vessel density and endothelial functionality throughout adulthood [49–52], which together result in the formation and growth of soft drusen centrally (Fig. 2). Drusen grow, because the RPE constitutively produces apolipoprotein B,E-containing lipoproteins and other material that normally exits to the circulation but is impeded in transit by aged BM-ChC. This “Oil Spill” hypothesis has compelling support from longitudinal clinical imaging and cell culture studies [53, 54]. ALSTAR2 study design explores this hypothesis by comparing structures and functions attributable to different layers of the neurovascular unit in aged normal eyes and in early AMD.

**Fig. 2 Fig2:**
[figure not shown]
Visual neuroscience of human retinal aging and age-related macular degeneration.Schematic shows log cone and rod density [30], choriocapillaris and retinal vessels, and helpful/ harmful factors for photoreceptor function and survival in the human macula. Soft drusen and basal linear deposits (gray) accumulate between choriocapillaris and retinal cells. They are thickest and confer highest risk for progression in central macula. Xanthophyll carotenoid pigment (orange) is highest in the foveal center (shown) with lateral extensions into the plexiform layers (not shown), plausibly attributable to the distribution of protective Müller glia [34]. The retinal capillaries and choriocapillaris are shown

Our vascular-metabolic model, because it is linked to the topography of retinal neurons, can be contrasted with (but does not exclude) mechanisms of AMD progression that have a pan-retinal or systemic basis (e.g., oxidative stress, inflammation, complement activation) [55, 56]. If our hypotheses withstand rigorous testing, strategies to maintain or restore health of ChC endothelium and/or BrM may have merit in protecting neurons, a winning strategy for tackling cerebrovascular disease and stroke. Our research plan, described below, seeks to identify specific changes in chorioretinal anatomy that are structural correlates for scotopic dysfunction including delayed RMDA. At the same time, we will also test cone-mediated vision to probe cone resilience and concurrently acquire specialized autofluorescence images for visualizing macular pigment (see Discussion).

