### Sample size determination and analysis plan

Each study aim will estimate the association between two continuous variables, visual function and structure (e.g., RMDA as measured by rod-intercept time and RPE thickness). Sample size requirements are based upon the calculation of correlation coefficients. Table 3 presents sample sizes required to have at least 80% power (alpha = 0.05) to detect a range of correlation coefficients as statistically significant. Because no published study uses specifically our proposed structure and function measures and our patient population, we used the literature reporting structure-function correlations ranging from 0.1–0.6 in aging and AMD to guide sample size estimation [86, 108–111]. Studies finding correlations > 0.3 typically address later stages of AMD (intermediate AMD and GA). Because we focus on early disease, we anticipate weaker structure-function relationships, ~ *r* = 0.2. Using these considerations as guides to compute sample size, 193 AMD and 193 normal patients are required in order to achieve statistical power of 80%. Given the longitudinal study design, we bolster this sample size for losses to follow-up over 3 years and the inability of some patients to perform some vision tests. Based on the ALSTAR1 experience [16, 71], we increase sample size by ~ 20% to address anticipated loss to follow-up. Thus, we enroll 240 each of persons in normal macula health and those with early AMD. We will also be including study of 20 young adults ages 20 to 30 years old to serve as a reference group, against which the older adults can be compared. They will participate in the same baseline protocol as the older adults.

**Table 3 Tab3:** Sample Size Determination in ALSTAR2

Pearson correlation coefficient for alternative hypothesis	Sample size required
0.2	193
0.3	84
0.4	46

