Statistical analyses will be conducted using SAS v. 9.4 (SAS Institute, Cary, NC) using a 2-sided alpha of 0.05. Although scientifically distinct, the 3 aims require similar analytical techniques, reflecting the underlying data structure being collected. A longitudinal study means that all primary measures will be collected at two points in time. However, for many measures, data will also be collected at specific retinal locations. Thus, statistical comparisons between structural and functional measurements must account for repeated measures and clustering of measurements within participants, i.e., eyes. The primary statistical tool to test hypotheses will be a mixed effects model. These models will be used to test both cross-sectional associations as well as prospective associations on changes in structure and function, both of which have hierarchical effects that need to be taken into account. The primary distinction between the models for cross-sectional and prospective associations is the inclusion of a time parameter in the latter. Prospective models will be used to explore the associations between joint changes in structural and functional measures but also whether baseline structural measures can predict functional changes. For example, considering the primary hypothesis for Aim 2A, i.e., RPE thickness is associated with scotopic dysfunction, the dependent variable will be RMDA and the main independent variables will be RPE volume (area x thickness across the macula) and mean normalized reflectivity. These measurements will be explored for their independent and joint effects on RMDA using unadjusted and adjusted models. For the cross-sectional analysis, the model will need to consider only the clustering of measurements within participants (i.e., at different locations). For the prospective analysis, a term must be added to the model to account for baseline and follow-up measurements.

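### The mixed model as described adjusts for clustering but does not separate within-eye from between-person association, so a single location-level structure coefficient cannot by itself support the topographic claim of Aim 1

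*Protocol article*

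**What the plan says.** The specific aims in the Background give Aim 1 a co-location hypothesis: "scotopic dysfunction will be accentuated where drusen and/or SDD are present". The same section promises that structure and function will be related topographically as well as cross-sectionally and over time. Later, under Background in physiology and aging (text after the Fig. 2 legend), the model is said to be one that "can be contrasted with (but does not exclude) mechanisms of AMD progression that have a pan-retinal or systemic basis". Methods, on two-color microperimetry, plans focal sensitivities matched to retinal structure. The Discussion presents the Center-Surround model, with topography as an explanatory variable, as something the data will test and refine.

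Under Sample size determination and analysis plan, the main tool is a mixed effects model, tested "using a 2-sided alpha of 0.05". In the Aim 2A example, for the cross-sectional analysis, "the model will need to consider only the clustering of measurements within participants (i.e., at different locations"; the prospective version adds a term for time. The predictors in that example are macula-wide RPE volume and mean reflectivity. Sample size rests on one correlation per person: "we anticipate weaker structure-function relationships", about r = 0.2, from which "193 AMD and 193 normal patients are required in order to achieve statistical power of 80" per cent.

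Dark adaptation is measured at two locations (5° and 12°) in one eye. Microperimetry in the same eye uses 23 targets according to the text and 21 according to the Fig. 4 legend.

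**The concern.** A random intercept gives an honest standard error when several locations come from one eye. It does not decide what the slope means. When a structural measure varies both between people and between locations, a single slope is a weighted average of the between-person slope and the within-eye slope. A process acting on the whole retina or the whole person, which worsens structure and function together, makes the first non-zero even when the second is zero.

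Aim 1 and the Center-Surround model need the second. If a significant single coefficient were offered as support for them, it could have come entirely from person-level association. That is the kind of explanation with which the article contrasts its own model.

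**Working it through.** **The plan's own figure.** The article gives "sample sizes required to have at least 80% power (alpha = 0.05": 193, 84 and 46 for r = 0.2, 0.3 and 0.4. The Fisher formula n = ((1.960 + 0.842)/atanh(r))² + 3 gives 193.97 for r = 0.2, that is 194; with the small bias term r/(2(n − 1)) it gives 193. The other two entries reproduce in the same way. For attrition, "we increase sample size by ~ 20% to address anticipated loss to follow-up", and 240 × 0.80 = 192. The sample size is sound for one correlation per person and is not affected by this point.

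**Inputs.** From the article: person-level r = 0.2; n = 193 (one group) or 386 (both groups pooled); m = 2 dark-adaptation locations, or m = 21 or 23 perimetry points; two-sided alpha 0.05. Assumed, because the article gives no value: the same intraclass correlation ρ for structure and function, 0.3, 0.5 or 0.7. The true within-eye slope is set to zero.

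**What the single slope estimates.** Take both measures standardised and the data balanced. Relative to within-eye information, the random-intercept model weights between-person information by W = (1 − ρ)/(1 − ρ + mρ). The expected single slope is

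b = W·m·rρ / [(m − 1)(1 − ρ) + W(1 − ρ + mρ)].

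Since W(1 − ρ + mρ) = 1 − ρ, the denominator is m(1 − ρ), and b = rρ/(1 − ρ + mρ). Its standard error is about 1/√(nm).

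- m = 2: b = 0.06/1.3 = 0.046 (ρ = 0.3); 0.10/1.5 = 0.067 (ρ = 0.5); 0.14/1.7 = 0.082 (ρ = 0.7).
- m = 23: b = 0.06/7.6 = 0.0079; 0.10/12 = 0.0083; 0.14/16.4 = 0.0085.

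With n = 193 and m = 2 the standard error is 1/√386 = 0.051. The expected z is then 0.046/0.051 = 0.91 to 0.082/0.051 = 1.62, and rejection is about 15% to 37%.

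**Simulation.** Random-intercept fits, 600 replicates per setting (Monte Carlo standard error at most about 2 percentage points):

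| Locations | n | Single slope significant, formula | Single slope significant, simulated |
|---|---|---|---|
| 2 | 193 | 15–37% | 14–37% |
| 2 | 386 | 25–63% | 25–64% |
| 21 or 23 | 193 | 8–9% | 7–10% |
| 21 or 23 | 386 | 12–13% | 12–14% |

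The within-eye coefficient was significant in 3–6% in every setting. Adding location terms to the single-slope model leaves these rates essentially unchanged, because location terms remove the average profile across locations and not the differences between people.

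**Sensitivity.** With person-level r = 0.4, an assumption above the protocol's planning value, the simulated rates are 50–91% (n = 193) and 72% to over 99% (n = 386) for two locations, and 18–26% and 31–42% for 21 or 23.

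**The worked example.** Macula-wide RPE volume has one value per eye and so no variation between locations. Its cross-sectional main-effect coefficient is wholly between-person. It is not a blend, and it carries no local information.

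**The case against.** The strongest case against is that the article gives no model equation. A single uncentred structure term is inferred, and centring may be specified in a fuller plan. The word only in the clustering sentence can fairly be read as saying that the cross-sectional model needs no time term, not as ruling out a within/between split. This stands, and it makes the point conditional on how structure is entered. It does not remove the point, because what the article does describe is not enough for the Aim 1 hypothesis.

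A reader might infer more: that a systemic process will be reported as local, or that the study cannot make its contrast at all. The documents do not support that. Nowhere is the coefficient said to be read as local, and the sentence announcing the contrast itself says that systemic mechanisms are not excluded. Only Aim 1 is worded as co-location. Aims 2 and 3 compare scotopic with photopic association, which this point does not touch.

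Several planned elements help, but none isolates the local association. The within-subject 5° versus 12° comparison sets function against function. Adjustment for age, smoking and CRP removes only measured person-level causes. Focal sensitivity matched to structure defines an outcome, not a model.

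Two limits on size also stand. On the perimetry grid, where focal matching is planned, the inflation is small. A two-location structural analysis is never spelled out, and OCT coverage at the outer spot is marginal: the volume is 25° high and so reaches 12.5°, while a 2° target at 12° extends to 13°.

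**Conclusion.** The point holds for analyses that enter a location-level structural measure as one term. Such a coefficient cannot by itself favour a local over a person-level explanation. At the protocol's own r of about 0.2, and with no local effect, it would be significant in 14–64% of studies with two dark-adaptation locations, depending on n and ρ. With 21 or 23 perimetry points the figure is 7–14%, against a nominal 5%.

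These figures rest on assumed intraclass correlations of 0.3–0.7, equal for both measures, and on balanced data without covariates or spatial correlation. Adjustment for person-level factors would lower them to the extent that those factors explain the shared variation. The prospective models were not quantified. This is a matter of specification and interpretation that should be settled before analysis; it does not invalidate the design.

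**What to change.** In every location-level model, enter structure as two terms, together with location terms:

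function(i, j) = location(j) + β_B × [eye mean of structure](i) + β_W × [structure(i, j) − eye mean(i)] + random intercept(i) + error.

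Rest any topographic claim (Aim 1, Center-Surround) on β_W. Report β_B as the person-level part, and report the difference between the two. Describe macula-wide predictors, such as RPE volume in Aim 2A, as person-level evidence only. If the full analysis plan already does this, one sentence saying so is enough.

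The change needs one extra term and no new data. Its price is precision. In the balanced setting above, the standard error of β_W is about 1/√(n(m − 1)), against 1/√(nm) for the single slope, a ratio of √(m/(m − 1)). That is √2 = 1.41 with two locations, but √(21/20) or √(23/22), both 1.02, on the perimetry grid. Where structure is the presence or absence of a deposit, eyes with none at any tested location add nothing to β_W, so the effective sample for the local test is smaller than the number enrolled.
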